## Abstract

•CARDIS tests a co-created web-based support programme for cardiac arrest survivors.•CARDIS has a randomised controlled design with a waiting list control group.•Tailored content addresses emotional, cognitive, and physical needs.•Primary outcome is wellbeing and health at 3 months post-enrolment.•Process evaluation explores adherence, social selection, and participant engagement.

CARDIS tests a co-created web-based support programme for cardiac arrest survivors.

CARDIS has a randomised controlled design with a waiting list control group.

Tailored content addresses emotional, cognitive, and physical needs.

Primary outcome is wellbeing and health at 3 months post-enrolment.

Process evaluation explores adherence, social selection, and participant engagement.

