### Outcomes and assessments

The primary outcome is overall wellbeing and health between the intervention and control groups 3 months after enrolment.

Secondary outcomes are self-reported HRQoL, life satisfaction, symptoms of depression and anxiety, PTSD, fatigue, cognitive impairment, sleep disturbances, and self-efficacy between the intervention and control groups 3- and 6-months after enrolment.

Assessments will be conducted at baseline, 3 months, and 6 months using self-reported validated digital questionnaires and study specific questions. Data completeness will be automatically monitored, and participants will receive regular reminders to ensure timely data entry. Variables are summarised in Table 3, Table 4.

**Table 3 t0015:** Data collection and assessments.

**Variables**	**Outcome measures**	**Baseline**	**3 months**	**6 months**

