### Sample size calculation and statistical analysis plan

The trial is planned to include 120 participants. A sample size calculation was conducted for the primary outcome variable (QWB). An a priori sample size calculation was conducted using G*Power for a repeated measures design with two groups and three time points (baseline, 3 months, and 6 months). Assuming a medium effect size (*f* = 0.25), a significance level of 5 % (*α* = 0.05), and a statistical power of 80 % (power = 0.80, corresponding to *β* = 0.20), the analysis showed that a total of 86 participants (43 per group) is sufficient to detect statistically significant differences between groups over time. To account for an estimated attrition rate of 30 %, a total of 120 participants (60 per group) will be recruited.

Baseline characteristics will be compared using chi-square, *t*-tests, or appropriate non-parametric methods. The intervention effect will be evaluated using linear mixed models (LMM) including fixed effects for time, group, and their interaction to assess differential changes over time between groups. Both random intercepts and slopes will be considered to account for individual variability in baseline levels and change over time.

All analyses will follow the intention-to-treat principle, whereby participants are analysed in their originally assigned groups regardless of adherence to the intervention.

There is no formally established minimal clinically important difference (MCID) for the QWB scale. However, previous research has shown that a total score below 50 is associated with clinically significant psychological distress.^58^ Effect sizes will be evaluated using marginal *R*^2^ and conditional *R*^2^.

Secondary outcomes will be analysed exploratorily. Although no formal power calculation has been conducted for these outcomes, their inclusion aims to provide a broader understanding of the potential effects of the intervention.

Adjustments for multiple comparisons, such as Bonferroni corrections, will be considered to control the risk of type I error.

No interim analyses are planned, as there are no anticipated safety concerns and the intervention does not involve clinical risk.

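### The primary outcome is the 3-month QWB difference, but the stated analysis is a group-by-time interaction over three visits and nothing ties the primary inference to month 3

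*Protocol article*

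**What the plan says.** The time point of the primary outcome is stated twice and consistently. The Abstract says "Primary outcome is wellbeing and health at 3 months post-enrolment". Outcomes and assessments says "The primary outcome is overall wellbeing and health between the intervention and control groups 3 months after enrolment". Table 3 names QWB as the instrument and schedules it at baseline, 3 and 6 months.

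The secondary outcomes in Outcomes and assessments are compared at both 3 and 6 months, but QWB is not in that list. Month-6 QWB is therefore collected without being called primary, secondary or exploratory.

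The section Sample size calculation and statistical analysis plan describes the analysis of the intervention effect as "linear mixed models (LMM) including fixed effects for time, group, and their interaction to assess differential changes over time between groups". On random effects it adds "Both random intercepts and slopes will be considered to account for individual variability in baseline levels and change over time". The sample size is for "a repeated measures design with two groups and three time points (baseline, 3 months, and 6 months"), with f = 0.25, a 5% significance level and 80% power. This gives 86 participants, raised to 120 for 30% attrition. The section does not name a month-3 contrast, does not say whether time is categorical or linear, and does not say which model term decides the trial.

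**The concern.** The outcome definition asks whether the groups differ at month 3. The analysis section asks whether the groups change differently over all three visits. An interaction over three visits can be significant because of month 6 alone, and it can miss a month-3 benefit that later fades.

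Fading is plausible here. Under Intervention group, the programme is used over a 3-month period, so the 6-month visit falls about three months after it ends.

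Several tests fit the printed wording: the joint interaction, a slope difference and the month-3 coefficient. On the same data they can disagree. If the choice is still open when results are seen, the 5% error rate of the primary claim is not protected.

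**Working it through.** **Inputs from the article.** Alpha 0.05, power 0.80, f = 0.25 (for two groups d = 2f = 0.5 SD), three visits, 1:1 allocation. Completers: 120 × 0.70 = 84, or n = 42 per group.

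**Assumptions.** The article gives no correlation between visits. I use compound symmetry with unit variance and ρ = 0.5, range 0.3 to 0.7. Effects δ3 and δ6 are group differences in SD at months 3 and 6, with none at baseline.

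**The plan's own figure.** The G*Power form for the group effect averaged over m = 3 visits has λ = f²·N·m / (1 + (m − 1)ρ). With N = 86 and ρ = 0.5, λ = 0.0625 × 86 × 3 / 2 = 8.06, and power on 1 and 84 df is 0.801. So 86 is reproduced. The within-between interaction form, λ = f²·N·m / (1 − ρ), needs only 28 at ρ = 0.5, or 82 under the alternative effect-size convention. The stated number thus matches a group effect averaged over baseline, 3 and 6 months, which is neither the interaction nor the month-3 difference.

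**Formulas for the comparison.**
- Joint interaction, time categorical: λ = n / (2(1 − ρ)) × [δ3² + δ6² − (δ3 + δ6)²/3], on 2 and 164 df, critical F 3.05.
- Change from baseline to month 3: noncentrality δ3 / √(4(1 − ρ)/n), 82 df.
- Baseline-adjusted month 3: noncentrality δ3 / √(2(1 − ρ²)/n), 81 df.

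**Effect at month 6 only (0, 0.5).** The bracket is 0.25 − 0.25/3 = 0.1667. At ρ = 0.5, λ = 42 × 0.1667 = 7.0 and power is 65%. At ρ = 0.3, λ = 30 × 0.1667 = 5.0 (50%). At ρ = 0.7, λ = 70 × 0.1667 = 11.67 (87%).

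**Fading effect (0.5, 0.25).** The bracket is 0.3125 − 0.1875 = 0.125. At ρ = 0.5, λ = 5.25 and power is 52%. The change contrast has noncentrality 0.5 / √(2/42) = 2.29, and the baseline-adjusted test 0.5 / √(1.5/42) = 2.65.

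**Month-3-only (0.5, 0) and sustained (0.5, 0.5).** Both brackets are again 0.1667, so the joint test has 65% power.

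| Effect at months 3, 6 (SD) | Joint 2-df | Month-3 change | Month-3 baseline-adjusted |
|---|---|---|---|
| 0, 0.5 | 65% (50–87) | 5% | 5% |
| 0.5, 0.25 | 52% (39–75) | 62% (48–83) | 74% (66–89) |
| 0.5, 0 | 65% (50–87) | 62% (48–83) | 74% (66–89) |
| 0.5, 0.5 | 65% (50–87) | 62% (48–83) | 74% (66–89) |

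Ranges are for ρ = 0.3 to 0.7.

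**Only if time were linear.** With visits at 0, 3 and 6 months, the slope contrast has weights (−1, 0, 1). A month-3-only effect then gives a slope difference of zero, detected at 5%, which is alpha. For a plateau (0, 0.5, 0.5), the fitted slope is 0.5/2 = 0.25 per 3 months. The fitted baseline difference is 0.333 − 0.25 = 0.083, where 0.333 is the mean of the three differences. The fitted group difference at month 3 is therefore 0.33 SD, and the fitted change from baseline is 0.25 SD, against a true 0.5.

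**The case against.** The article gives model terms and a purpose. It gives no omnibus test and no success rule. With categorical time, the same interaction contains the baseline-to-month-3 coefficient, so the model can answer the primary question as it stands. A separate analysis plan may name that coefficient. All this is fair, and it limits the point to the missing link between outcome and test. It does not remove the point: the article itself states an inferential purpose and a sizing basis over three visits that differ from its own outcome definition. A later document naming month 3 would have to depart from that text.

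Three stronger readings are tempting but not supported.

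- A reader might infer that the random-slope sentence means linear time, so that month 3 gets no weight. The coding of time is not stated, slopes are only to be considered, and a random slope can sit beside a categorical fixed effect of time. The linear-time results are conditional.
- A reader might infer that the joint test generally misses month-3 effects. For a month-3-only or sustained effect it is about equal to the change contrast (65% against 62%). It loses power when the effect fades, or relative to a baseline-adjusted test.
- A reader might count the open random-effects structure as a fault. That is detail an article may leave to the analysis plan.

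**Conclusion.** The point holds in this form: the primary outcome is fixed at month 3, the stated analysis is a group-by-time comparison over baseline, 3 and 6 months, and no sentence connects them. Confidence is high on the missing link. It does not extend to which test the team intends.

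The main consequence is one of meaning. A significant joint interaction is not evidence of a month-3 effect, since it arises in about two trials in three when a 0.5 SD effect exists at month 6 only. The second consequence, lost power, depends on the effect's shape and on the comparator: 52% against 62% or 74% when the effect fades. These sizes rest on 84 completers, compound symmetry and a correlation that the article does not give.

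**What to change.** State one primary test: the between-group difference in QWB at month 3, estimated from the linear mixed model with time as a categorical fixed effect and baseline adjusted for or constrained equal between groups, two-sided 5%, with a 95% confidence interval. List QWB at month 6 as a secondary outcome. Report the joint interaction as supportive only. The covariance and random-effects choice can stay with the analysis plan.

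The wording takes a few sentences and no new data. Trial status places the start of main recruitment in autumn 2026, so there is time. It also says that amendments need ethics approval and an entry in the registry.

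The real cost is that the 80% power must be restated for this contrast. With 84 completers and d = 0.5, an unadjusted month-3 comparison has noncentrality 0.5 / √(2/42) = 2.29 and about 62% power. The baseline-adjusted test has 74% at ρ = 0.5 (66 to 89% for 0.3 to 0.7).

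By the normal approximation, 80% power needs 2 × (1.96 + 0.84)² / 0.25 = 62.7, so 63 per group: 126 completers, and 126 / 0.70 = 180 recruited. With baseline adjustment at ρ = 0.5 it needs 62.7 × 0.75 = 47.0, about 48 per group: 96 completers, and 96 / 0.70 = 137.1, so about 138 recruited. Both fit the flow given under Study design and setting, about 170 a year or 255 in 18 months. The team should either raise the target or state the lower power, with the correlation it assumes.

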### Eligibility criteria

Inclusion: ≥18 years of age, survived cardiac arrest 1–3 months prior to enrolment, access to internet-enabled device.

Exclusion: insufficient linguistic or cognitive ability to engage with the intervention or complete questionnaires designed in Swedish, or concurrent participation in another study collecting patient-reported outcome measures (PROMs) as primary endpoints.

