### Intervention group

Participants allocated to the intervention group will receive access to the web-based support programme (https://www.hjartstoppsoverlevare.se) in addition to receiving a printed informational booklet, one-time individual self-management advice and standard post-cardiac arrest care, as defined by current clinical guidelines.^37^, ^38^ The programme is self-guided and designed to be used flexibly, allowing participants to engage with the content according to their individual needs and pace over a 3-months period. Participants are permitted, but not required, to involve a key family member when taking part of the programme.

To promote adherence, participants allocated to the intervention group will receive automated reminders every third week encouraging continued engagement with the digital support programme throughout the access period.

The intervention is grounded in the concept of self-care maintenance, which refers to behaviours aimed at promoting well-being, preserving health, and maintaining physical and emotional stability.^57^ During the intervention, participants are encouraged to set personal goals and create a health plan for their rehabilitation aligned with the programme’s focus areas. Key content is listed in Table 2.

**Table 2 t0010:** Key content in the support programme promoting self-care maintenance.

*Cognitive support*	Information material on common cognitive sequelae (e.g., attention, memory, executive function) and strategies for managing them.
*Emotional support*	Guidance on emotional challenges such as anxiety, depression, post-traumatic stress disorder, fatigue, and sleep disturbances, with suggested exercises in relaxation, breathing, mindfulness, and socialisation.
*Physical rehabilitation*	Education on physical activity and its role in recovery, including practical guidance delivered via video and lectures. The module also highlights the risk of kinesiophobia – fear of movement or physical exertion – which may hinder rehabilitation.
*Lifestyle support*	Guidance on nutrition, alcohol, and nicotine use, with exercises in smoking cessation, alcohol reflection, and healthy eating habits.
*Relationships*	Encouragement to re-establish intimate and social connexions, including exercises to reflect on relationship changes, rebuild social confidence, and explore intimacy with partners.

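### The random-effects structures named for the QWB model tie the variance of change to month 3 to that of change from month 3 to month 6, so the month-3 standard error can be biased in either direction; an unstructured covariance removes the restriction cheaply

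*Protocol article*

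**What the plan says.** Under *Outcomes and assessments* the protocol article sets the primary comparison: "The primary outcome is overall wellbeing and health between the intervention and control groups 3 months after enrolment". On timing, the same section says "Assessments will be conducted at baseline, 3 months, and 6 months using self-reported validated digital questionnaires and study specific questions", and Table 3 lists the QWB at all three visits.

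*Sample size calculation and statistical analysis plan* names the analysis as "linear mixed models (LMM) including fixed effects for time, group, and their interaction to assess differential changes over time between groups", followed by "Both random intercepts and slopes will be considered to account for individual variability in baseline levels and change over time". It does not say whether time is linear or categorical, which residual covariance applies, or how the final random-effects structure will be chosen.

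Two design features bear on how variable change may be. Participants must have "survived cardiac arrest 1–3 months prior to enrolment", and the intervention group may "engage with the content according to their individual needs and pace over a 3-months period".

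**The concern.** The confidence interval and p-value for the primary month-3 contrast depend on the modelled variance of change from baseline to month 3. With equally spaced visits and independent, equal-variance residuals, both a random intercept and a random intercept plus linear slope tie that variance to the variance of change over the next three months. If the two differ in truth, the standard error at the primary time point is off. Too small, and the test exceeds its nominal 5%; too large, and power is lost. Choosing between the two structures by model fit does not help, because both carry the restriction.

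The design gives some reason to doubt equality. Baseline falls early in recovery, and programme access, used at each person's own pace, fills the first interval. Both could make change before month 3 more heterogeneous than change after it.

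**Working it through.** **Inputs from the protocol article.** Visits at 0, 3 and 6 months; primary contrast at month 3; fixed effects for time, group and their interaction; random intercepts and slopes; f = 0.25, α = 0.05, power 0.80, 86 evaluable participants. **Not given, therefore assumed:** QWB standard deviations (SDs), between-visit correlations, residual covariance and coding of time.

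**1. The plan's own figure.** The repeated-measures between-groups test with m = 3 visits and an assumed common correlation ρ = 0.5 has noncentrality f²·N·m/(1+(m−1)ρ) = 0.0625 × 86 × 3/2 = 8.06 on 1 and 84 degrees of freedom, giving power 0.801. So 86 is reproduced. That calculation uses one correlation for all pairs of visits and so does not tell us whether the pairs differ.

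**2. What the two structures imply.** Let σ² be the residual variance and σ_b² the slope variance per month.
- Random intercept: all three pairwise changes have variance 2σ².
- Random intercept plus linear slope: Var(Y3−Y0) = Var(Y6−Y3) = 9σ_b² + 2σ², and Var(Y6−Y0) = 36σ_b² + 2σ².

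Both therefore set Var(Y3−Y0) = Var(Y6−Y3).

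**3. Effect on the month-3 standard error.** Take equal unit SDs, visit as a factor in the fixed effects and complete data. The true variance of a change is D = 2(1−r). In the cases below, Gaussian-likelihood fits show that the intercept model estimates the mean of D(0–3), D(3–6) and D(0–6), and the slope model estimates the mean of D(0–3) and D(3–6). For the group difference in change to month 3:
- SE ratio (model/true) = √(fitted variance / D(0–3))
- type I error = 2[1 − Φ(1.96 × ratio)]

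Example, correlations (0–3 / 0–6 / 3–6) of 0.5/0.4/0.7: D(0–3) = 1.0, D(3–6) = 0.6, D(0–6) = 1.2.
- Intercept: (1.0 + 0.6 + 1.2)/3 = 0.933; ratio √0.933 = 0.966; type I error 5.8%.
- Slope: (1.0 + 0.6)/2 = 0.8; ratio √0.8 = 0.894; type I error 8.0%.

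| Correlations 0–3 / 0–6 / 3–6 | D(0–3), D(3–6), D(0–6) | Intercept: ratio (type I) | Intercept + slope: ratio (type I) |
|---|---|---|---|
| 0.6/0.6/0.6 (compound symmetry) | 0.80, 0.80, 0.80 | 1.00 (5.0%) | 1.00 (5.0%) |
| 0.6/0.36/0.6 (AR(1)) | 0.80, 0.80, 1.28 | 1.10 (3.2%) | 1.00 (5.0%) |
| 0.6/0.5/0.65 | 0.80, 0.70, 1.00 | 1.02 (4.5%) | 0.97 (5.8%) |
| 0.6/0.5/0.7 | 0.80, 0.60, 1.00 | 1.00 (5.0%) | 0.94 (6.7%) |
| 0.6/0.4/0.7 | 0.80, 0.60, 1.20 | 1.04 (4.1%) | 0.94 (6.7%) |
| 0.5/0.4/0.7 | 1.00, 0.60, 1.20 | 0.97 (5.8%) | 0.89 (8.0%) |
| 0.5/0.45/0.8 | 1.00, 0.40, 1.10 | 0.91 (7.4%) | 0.84 (10.1%) |
| 0.7/0.5/0.6 | 0.60, 0.80, 1.00 | 1.15 (2.4%) | 1.08 (3.4%) |
| 0.75/0.45/0.5 | 0.50, 1.00, 1.10 | 1.32 (1.0%) | 1.22 (1.6%) |

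Rows three to seven have the more variable early change, the last two the more variable late change.

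**4. Sensitivity.** Unequal SDs move the figures: 0.6/0.5/0.7 with SDs 1, 1.1 and 1.2 gives 4.0% (intercept) and 5.6% (slope). If the contrast is the group difference in level at month 3 rather than in change, the effect is smaller. Over ten equal-SD patterns (compound symmetry, AR(1), early- and late-variable) the intercept model was exact and the slope model's ratio lay between 0.94 and 1.00, a type I error of at most 6.5%.

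**The case against.** The strongest reply is that the article does not fix what is criticised. It says only that intercepts and slopes will be considered. Linear time and independent, equal-variance residuals are supplied by the reader, and a heterogeneous or unstructured residual covariance would be compatible with the wording and would lift the restriction. Such detail often sits in a statistical analysis plan, and none is shown here. This stands as a limit: the restriction is conditional on the default residual structure. It does not remove the point, because random effects are the only covariance device the article names.

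A related reply is that slopes could be attached to visit as a factor. That model has seven variance parameters for a covariance matrix with six elements, so the split between random effects and residual is not identified and some software will refuse it. Where it can be fitted, the marginal covariance is unrestricted and the month-3 standard error is not affected.

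A reader might also infer that the standard error is wrong and most likely too small, or that the test exceeds 5% whenever early change is the more variable. The documents support neither. They contain no QWB variance or correlation. Enrolment timing and the access period make early heterogeneity plausible but do not measure it. Under compound symmetry there is no error, and under AR(1) the slope model is exact. With more variable early change the intercept model can still be exact (0.6/0.5/0.7) or conservative (0.6/0.4/0.7), because it averages all three change variances. The larger figures also need a wide gap between the 0–3 and 3–6 correlations; milder gaps give under 6% with the slope model.

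**Conclusion.** The point holds as a conditional weakness with an inexpensive remedy, not as a demonstrated error. Given independent, equal-variance residuals and a random intercept with or without a linear slope, the model imposes an equality between the two three-month change variances that nothing in the protocol justifies, and the primary test depends on it. The size is unknown because QWB variances and correlations are not reported; over the assumed values the bias runs from 16% too small to 32% too large. With equal SDs, the slope model understates the standard error of the change contrast if early change is the more variable; the intercept model may then be anti-conservative, correct or conservative.

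**What to change.** For the primary analysis, replace the random-effects sentence with: visit as a factor (0, 3 and 6 months); group-by-visit fixed effects; an unstructured 3×3 within-participant covariance; REML with Kenward-Roger degrees of freedom; the month-3 group contrast as the primary test; no data-driven choice of random effects. Name a fallback covariance in advance for non-convergence, for example heterogeneous Toeplitz, with robust standard errors. Treating visit as a factor also settles the coding of time: a linear group-by-time term would force the month-3 difference in change to be half the month-6 difference.

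The cost is small. The unstructured matrix has six parameters against two (intercept) or four (intercept plus slope), which 84 completers (120 less 30%) can readily support. The confidence interval may be slightly wider. *Trial status* reports a pilot phase with recruitment to start in autumn 2026, so the model can be fixed before then.

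### Marginal and conditional R² are named as the effect-size measures, but neither isolates the 3-month difference between groups, shows its direction or is in QWB points

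*Protocol article*

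**What the plan says.** The protocol article, under *Outcomes and assessments*, makes the primary outcome a comparison of arms at one time point: "The primary outcome is overall wellbeing and health between the intervention and control groups 3 months after enrolment". Table 3 assigns the Questionnaire on Well-Being (QWB) to it, measured at baseline, 3 and 6 months.

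Under *Sample size calculation and statistical analysis plan*, the intervention effect is to be evaluated with "linear mixed models (LMM) including fixed effects for time, group, and their interaction to assess differential changes over time between groups". On the random part it says: "Both random intercepts and slopes will be considered to account for individual variability in baseline levels and change over time". It then notes: "There is no formally established minimal clinically important difference (MCID) for the QWB scale". After a remark on a QWB score associated with distress, it fixes the measure of effect size: "Effect sizes will be evaluated using marginal *R*^2^ and conditional *R*^2".

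The article names no other measure of effect size for the analysis. The sample size calculation uses Cohen's f = 0.25, which is a planning input.

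**The concern.** An effect size in a randomised trial should say how far apart the arms are, and in which direction, at the time point that matters. The two R² statistics answer another question: how much of the total variation in QWB the whole model accounts for. Time is one of the fixed effects, so any change shared by both arms counts towards marginal R². The random effects count towards conditional R², so stable differences between patients count there too.

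This matters here for two reasons. Patients enter 1 to 3 months after the arrest (*Eligibility criteria*), so change in both arms during follow-up is plausible. And because the article says the QWB has no established threshold for a clinically important difference, readers will lean on the reported effect size to judge benefit. A conditional R² near 0.5 could be taken for a large effect when it reflects little more than the correlation between a patient's repeated scores.

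**Working it through.** **The plan's own figure.** The plan gives no R² value to reproduce. Its only effect-size figure is f = 0.25 in the sample size calculation. With a between-factors repeated-measures F test, m = 3 time points and an assumed correlation ρ = 0.5 (not stated in the article), λ = N·f²·m / (1 + (m − 1)ρ) = 86 × 0.0625 × 3 / 2 = 8.06. On 1 and 84 degrees of freedom, power is 0.8015, which agrees with the stated 86. R² enters nowhere.

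**Inputs.** From the article: two arms, 1:1 allocation, three time points, and fixed effects for time, group and interaction. Assumed, because the article gives no QWB SD, correlation or recovery course: total SD 1, time as three categories, and a random intercept only. Intercept and residual variance are 0.5 each (intraclass correlation, ICC, 0.5) unless varied.

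**Formulas.** Let V be the variance of the six cell means (two arms by three times).

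- Marginal R² = V / (V + 1)
- Conditional R² = (V + ICC) / (V + 1)

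Let both arms recover by a at 3 months and b at 6 months, and let the programme add δ at both. With V₀ = (a² + b²)/3 − (a + b)²/9, the cell means give

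V = V₀ + δ(a + b)/9 + 2δ²/9.

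The middle term multiplies programme effect by recovery, so the same δ adds a different amount to V under a different natural course.

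**Results at ICC 0.5** (SD units)

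| Shared recovery a/b | Programme effect δ | V | Marginal R² | Conditional R² |
|---|---|---|---|---|
| 0/0 | 0 | 0 | 0 | 0.500 |
| 0.2/0.3 | 0 | 0.0156 | 0.015 | 0.508 |
| 0.3/0.5 | 0 | 0.0422 | 0.041 | 0.520 |
| 0.4/0.6 | 0 | 0.0622 | 0.059 | 0.529 |
| 0.5/0.8 | 0 | 0.1089 | 0.098 | 0.549 |
| 0/0 | +0.5 | 0.0556 | 0.053 | 0.526 |
| 0/0 | −0.5 | 0.0556 | 0.053 | 0.526 |
| 0.4/0.6 | +0.5 | 0.1733 | 0.148 | 0.574 |
| 0.4/0.6 | −0.5 | 0.0622 | 0.059 | 0.529 |
| 0.5/0.8 | +0.5 | 0.2367 | 0.191 | 0.596 |

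Worked line, 0.4/0.6 with δ = +0.5: V = 0.0622 + 0.5 × 1.0/9 + 2 × 0.25/9 = 0.0622 + 0.0556 + 0.0556 = 0.1733 (unrounded). Marginal R² = 0.1733/1.1733 = 0.148.

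**Reading the table.**

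1. With no programme effect, marginal R² runs from 0.015 to 0.098 according to shared recovery alone.
2. One and the same 0.5 SD benefit gives 0.053, 0.148 or 0.191, according to recovery.
3. Without recovery, benefit and harm of equal size cannot be told apart. At 0.4/0.6 SD recovery, a 0.5 SD harm happens to give the same values as no effect, because −0.5 × 1.0/9 cancels 2 × 0.25/9.
4. With no effect of any kind V = 0, and conditional R² equals the ICC: 0.30, 0.50 or 0.70 at ICC 0.3, 0.5 or 0.7.

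**Does the planned model supply a better measure?** Yes. In 200 simulated trials of 60 per arm at ICC 0.5, the fitted between-group contrast in change to 3 months averaged about 0.01 SD where the truth was 0 (recovery 0.5/0.8), and 0.48 SD where the truth was 0.5 (no recovery).

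**The case against.** The strongest reply is that the treatment effect is assessed elsewhere in the same section. The mixed model's group-by-time term is signed and on the QWB scale, and nothing says it will go unreported. R² may be meant only as a supplementary summary, and a condensed article may leave the reporting format to an analysis plan that is not shown. Much of this stands. It would be wrong to infer that the trial will not report a mean difference, or that its primary test is compromised. What remains is that the article does not leave the effect-size measure open. It names one, and that one does not measure the difference between arms.

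Two stronger readings are tempting, and the documents support neither.

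- **That R² says nothing about the intervention.** Marginal R² includes the group and interaction terms. For any δ above zero and any net shared recovery of zero or more, the formula for V shows that it rises.
- **That a useless programme would outscore an effective one.** Setting no effect with 0.4/0.6 SD recovery (0.059 and 0.529) beside a 0.5 SD benefit with no recovery (0.053 and 0.526) gives that order, but only by assigning the two programmes different natural courses. Under the same recovery the order is 0.148 against 0.059 in favour of the effective programme. Under one shared course, reversal would need a natural decline that the programme partly offsets (for example 0.084 against 0.098 with declines of 0.5/0.8 SD). The article gives no basis for assuming one.

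**Conclusion.** The point holds as a wrongly chosen measure of effect size. Marginal and conditional R² describe the whole model. They mix recovery common to both arms and variance between patients with the group contrast that the article makes primary, and they carry no sign and no QWB units. From the reported figure alone, a reader could not tell how much is recovery and how much is programme.

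The numerical size rests on assumed values: SD 1, a random intercept only and the recovery courses shown. Other values would move the figures. That the two statistics are unsigned and cover the whole model does not depend on those assumptions.

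The fault is confined to how the size of benefit is expressed. The model, its test of the interaction, the type I error, the intention-to-treat analysis and the sample size are untouched.

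**What to change.** Replace the R² sentence under *Sample size calculation and statistical analysis plan* with:

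> The effect size is the model-based between-group difference in mean QWB at 3 months (and at 6 months) with 95% CI, in QWB points and as a standardised difference.

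State which SD is used for standardising. If R² is wanted, keep it in a separate sentence as a description of model fit.

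The cost is one sentence. The planned model already yields these estimates, and no new data, extra patients or change of model are needed. *Trial status* puts the start of main recruitment in autumn 2026 and sets the route for amendments (ethics approval and a registry entry), so the change can be made well before outcome data are analysed.
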